## Introduction

As a result of one donation, whole blood donors lose 8% (men) to 81% (menstruating women) of their total iron stores [1–3]. High donation frequency increases the risk for depleted iron stores through the haemoglobin (Hb)-bound iron loss and subsequent increased erythropoiesis [4, 5]. Depletion of iron stores, iron-deficient erythropoiesis and iron-deficiency anaemia may not only negatively influence donor health [6], but may also lead to a higher risk of low-Hb deferral [7], which is demotivating for a blood donor and costly for blood banks [8]. Most blood banks monitor donors’ Hb levels and defer donors with Hb levels below a certain threshold, aiming to avoid anaemia, minimise low-Hb deferral and ensure sufficient Hb content for transfusion [9]. However, these Hb levels do not reflect the donors’ iron status [5, 10] and the World Health Organization advises the monitoring of serum ferritin to detect iron deficiency [11].

Iron deficiency in whole blood donors can be prevented by extending donation intervals or providing iron supplements [5, 9, 12]. Extending donation intervals might be the preferred method in light of possible gastrointestinal disturbances as a result of iron supplementation, poor compliance or negative perceptions of taking iron tablets [12]. Previous studies have shown that prolonged donation intervals are associated with lower risk of low-Hb deferrals [8, 13]. Additionally, the results from the randomised-controlled INTERVAL trial have shown that donating at 8-week intervals for men and 12-week intervals for women lead to significantly lower Hb and ferritin concentrations than those observed in longer donation interval groups (i.e. 12-week intervals and 16-week intervals for men and women, respectively) [8].

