### Control condition

Before each whole blood donation, a donor is seen by one of the doctors or nurses to check haemoglobin levels and blood pressure and screen for any indications a donor might not be eligible to donate whole blood at that moment. Sanquin’s current guidelines include Hb cut-offs for donor eligibility of > 13.5 g/dL for men and > 12.5 g/dL for women, which is in accordance with the international guidelines and European legislation [15]. Donors with low Hb (measured prior to donating in capillary blood with HemoCue 201, Angelholm, Sweden) are deferred from donating for 3 months.

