### Data collection

Pseudonymized data on age, sex, Hb levels and deferrals will be extracted from the donor database (eProgesa software application; MAK-SYSTEM) for all new and repeat whole blood donors who visit a fixed blood collection centre during a pre-selected week at one of the three measurement time points and gave consent for their information and left-over material to be used for research purposes. Furthermore, we will calculate donor return rates as the percentage of donors with a donation attempt within 6 months after the next allowed donation date. We will use stored plasma samples of new donors and repeat donors who made a donation attempt at one of the fixed blood collection centres during one of the pre-selected measurement time points to determine ferritin levels in intervention and control groups. Ferritin will be measured on the Architect i2000sr (Abbott Diagnostics) from donation samples collected in K3EDTA tubes (Greiner) and stored at − 30 °C. After storage, ferritin levels may be lower than those in fresh samples [16]. Within the FIND’EM study, we will compare ferritin levels of donors donating at centres where the ferritin-guided donation interval policy was implemented to ferritin levels of donors donating at centres where the policy was not implemented yet. For both groups, we will use samples that were stored for the same time period. Therefore, we expect similar decreases of ferritin levels as a result of storage in both groups, still allowing this comparison. For the validation of ferritin levels from stored samples of donors participating in the FIND’EM study, we will compare ferritin levels from stored samples with ferritin levels measured in fresh samples as part of the ferritin-guided donation interval policy.

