### Sample size calculations

Using data from the first clusters of blood collection centres that have implemented the ferritin-guided donation intervals, we found a mean increase in ferritin levels of 4 ng/mL (standard deviation (SD) 54 ng/mL) over a 6-month period. To detect a difference of 4 ng/mL, assuming a SD of 54 ng/mL, a two-sided significance level of 5%, a power of 80% and ignoring the correlated observations, a sample size of 5720 subjects is needed. We used the following formula to calculate the actual sample size:
$$ m=\frac{N}{1+\left(n-1\right)\left(1-\rho \right)} $$

where *m* = number of blood collection centres, *N* = sample size ignoring the correlated observations; *n* = average number of subjects within a blood collection centre and *ρ* = intraclass correlation coefficient. Assuming an average number of subject within each blood collection centre of 150 and an intraclass correlation coefficient of 0.1, we need 42 centres in total. With the fixed number of 50 blood collection centres (i.e. 7500 subjects), the power of the study is more than enough to detect the difference of 4 ng/mL. An individual autocorrelation coefficient is not included in our sample size calculation as we include repeated cross-sectional measures. With approximately 7500 donation attempts at fixed collection centres each week, we anticipate that we will be able to collect data on age, sex, Hb levels and deferrals and ferritin levels of approximately 7500 donors at baseline, mid-implementation and after implementation, thereby including more than sufficient data to reliably investigate the effectiveness of the ferritin-guided donation intervals. Furthermore, during data collection at mid-implementation, approximately 3500 donors filled in the questionnaires. We expect about the same response for the data collection after full implementation of the new policy.

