### Data analyses

Descriptive statistics will be provided for the donor population at baseline, mid-implementation and after full implementation. Linear mixed models (i.e., multilevel analysis) will be used to investigate differences in Hb and ferritin levels, low-Hb deferral, donor return rates and donor health between intervention and control groups using data collected at baseline, mid-implementation and after implementation. Two-level models with donors nested within blood collection clusters will be fitted, with a random intercept for cluster to adjust for the correlation between measurements of donors within the same cluster. All models include a binary variable indicating whether the observation was done before or after the start of the intervention and will be adjusted for the time point of implementation of the policy (fixed variable, time in months since the start of implementation period). Because of the nature of our outcome measures and because we include a new sample of donors at every measurement time point, we do not expect robust methods to be appropriate for sensitivity analyses. To investigate how the impact of ferritin-guided donation intervals develops over time, the latter will also be included as an effect modifier [14]. An intention-to-treat approach will be used and stratified analyses will be performed to investigate differences in the effectiveness of ferritin-guided donation intervals for male and female donors.

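### The stated Hb model uses no earlier Hb value of the donor, although the donor database very probably holds one for most repeat donors; adding it would sharpen the Hb estimate by an amount the documents cannot fix

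*Protocol article*

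**What the plan says.** Under Data analyses, the article describes two-level linear mixed models, donors within clusters, for all outcomes. On the fixed part it says "All models include a binary variable indicating whether the observation was done before or after the start of the intervention", with further adjustment for time in months and a cluster random intercept. Analyses stratified by sex are planned. No earlier donor measurement is mentioned.

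Under Data collection, "Pseudonymized data on age, sex, Hb levels and deferrals will be extracted from the donor database" for donors who visit a fixed centre in a selected week at one of three time points. Earlier visits of those donors are neither listed nor excluded.

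Under Control condition, "Before each whole blood donation, a donor is seen by one of the doctors or nurses to check haemoglobin levels". The Setting section adds Hb testing at the screening of new donors. The return rate under Data collection needs attempt dates, and the policy counts every fifth donation, so some donation history must be stored.

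**The concern.** Hb is a named outcome in the Research objectives, and a donor's own earlier Hb is usually a good predictor of the present one. A value taken before November 2017 precedes the policy everywhere, so adjusting for it does not condition on a consequence of the intervention. Drawing a new cross-section at each wave does not prevent linking a sampled donor to that donor's earlier visits.

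What is at stake is precision. Of the three waves, only mid-implementation has exposed and unexposed clusters side by side, so the contrast rests heavily on it. The extraction also has to be settled ahead of the analysis: no analysis plan can adjust for values that were not pulled.

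**Working it through.** **1. The plan's own figure.** The only sample size calculation is for ferritin: "To detect a difference of 4 ng/mL, assuming a SD of 54 ng/mL". Total N = 2 × 2 × (1.960 + 0.842)² × 54² / 4² ≈ 5722, against the stated 5720. The printed formula gives 5720 / (1 + 149 × 0.9) = 42.3, against the stated 42 centres. Both reproduce. Neither concerns Hb, and whether that formula suits this design is a separate question.

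**2. Inputs from the article.**
- 29 clusters and three waves.
- About 7500 donors per wave, so 7500 / 29 ≈ 259 per cluster and wave.
- Clusters exposed: 0 at baseline; 8 + 4 + 4 = 16 at mid-implementation (16 / 29 = 55%, as stated); 29 at the end.
- ICC 0.1, given for ferritin.

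**3. Inputs that the article does not give (assumed).**
- Correlation r of Hb with the donor's earlier Hb: 0.4 to 0.6.
- Share s of donors with an earlier value: 0.8 to 1.0.
- ICC for Hb: 0.01 to 0.10.
- Cluster autocorrelation (CAC): 0.8 to 1. The planned model, with a cluster intercept only, implies 1. The Discussion says this quantity was left out of the sample size.

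**4. Residual variance removed.** g = s × r². The low end is 0.8 × 0.4² = 0.128 and the high end is 1.0 × 0.6² = 0.36.

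**5. Effect on the variance of the policy estimate.** With total variance 1, a cluster's three wave means have covariance ICC·CAC between waves, and variance ICC + (1 − ICC)(1 − g)/259 within a wave. The generalised least squares variance of the policy effect, with wave as a category, was computed with and without g. Fitting time as linear months gave essentially the same percentage reductions.

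| ICC | CAC | Reduction, g = 0.128 | Reduction, g = 0.36 |
|---|---|---|---|
| 0.01 | 1 | 12.3% | 34.8% |
| 0.10 | 1 | 12.7% | 35.9% |
| 0.05 | 0.9 | 5.3% | 14.9% |
| 0.10 | 0.95 | 5.2% | 14.6% |
| 0.10 | 0.9 | 3.2% | 9.1% |
| 0.10 | 0.8 | 1.8% | 5.1% |

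The gain carries over almost one for one when CAC is 1. It shrinks quickly once clusters drift from wave to wave, because the covariate is taken here to reduce only donor-level variance.

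**6. Who attends.** The policy defers repeat donors with low ferritin for 6 or 12 months, so it changes who is present in a survey week. As an illustration with assumed values, suppose the lowest 15% on ferritin are absent in exposed clusters, ferritin correlates 0.4 with both present and earlier Hb, the two Hb values correlate 0.5, and nobody's Hb changes. Mean ferritin among attenders rises by 0.2332 / 0.85 = 0.274 SD. The unadjusted Hb difference is 0.4 × 0.274 ≈ 0.11 SD. After adjustment, about 0.11 − 0.5 × 0.11 ≈ 0.055 SD remains. The two estimates therefore answer somewhat different questions.

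**The case against.** The strongest reply is that this is an unlisted covariate and not an error. The sentence on model content sets a minimum. Age and sex are extracted without being named as covariates, so the article evidently does not list everything, and a fuller plan may do so. This stands to the extent that the point is an efficiency improvement. It does not dispose of the point, because the article does state the models and the extraction, and neither provides for an earlier Hb.

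A reader might infer that the extraction is confined to the survey-week visit. The text does not say this: the week defines which donors are included, and the return rate needs attempts outside it. A reader might also infer that every repeat donor has a pre-policy Hb. Donors registered after November 2017 have at most a screening value, and donors at their screening visit have no earlier value at all. That the database holds the older values is itself an inference.

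It is also fair to say that the baseline wave and the cluster intercept already deal with stable differences between clusters in starting Hb, so the case does not rest on imbalance. Finally, adjustment is not purely a gain in precision. Part of the change in composition that it removes is a consequence of the policy, which matters most for the low-Hb deferral rate. That stands, and it is why the unadjusted results must be kept.

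**Conclusion.** The point holds as a modest, inexpensive improvement to the Hb analysis. Under the planned random-intercept model the variance of the Hb effect would fall about 12 to 36%; with ICC 0.1 and cluster autocorrelation 0.8 to 0.95, about 2 to 15%. Both ranges assume r = 0.4 to 0.6 and an earlier value for 80 to 100% of donors. The article gives no within-donor Hb correlation, Hb ICC or share of repeat donors, so no single figure can be defended. The top of the range needs r = 0.6, full coverage and no cluster drift all at once. By the last wave, planned for the end of November 2019, a pre-policy value is at least two years old, so r may be lower there.

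A reader might conclude that the planned Hb estimate is biased or that the trial is underpowered for Hb. The documents support neither. A reader might also extend the gain to ferritin through earlier donation frequency, since the Introduction says "High donation frequency increases the risk for depleted iron stores". Nothing in the documents allows that to be sized, and it is not claimed.

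**What to change.** - **Extraction.** For repeat donors in the survey weeks, also extract the last Hb before November 2017. For the baseline wave, take the last Hb before the index week. For donors registered later, take the screening Hb.
- **Hb model.** Add this value with a slope for each wave, since the time lag differs. Give donors at pre-donation screening a new-donor indicator, or analyse them separately.
- **Reporting for Hb.** Show the unadjusted estimate beside the adjusted one, and state that the unadjusted contrast includes the change in who attends while the adjusted one partly removes it.
- **Low-Hb deferral.** Keep the unadjusted rate as the main result and give the adjusted one as supportive.

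The choice should be written down before the outcome data are analysed. The cost is a wider query of a database already in use and a few sentences in the analysis section. The downside is an older, less correlated earlier value in the last wave.

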### Study population

Both new (i.e. a donor undergoing pre-donation screening) and repeat donors (i.e. a donor making a whole blood donation or attempt) are eligible to participate in this study. The intervention likely results in delayed effects. Ferritin levels of a donor visiting a blood collection centre where the intervention has been implemented will only be measured every fifth donation. Furthermore, the extension of donation intervals makes it necessary to allow the blood collection centres to be exposed to the intervention for a certain amount of time before donors return and the effectiveness of the new policy becomes observable. We therefore selected three measurement time points: (1) before implementation (i.e. baseline), (2) mid-implementation (when 55% of blood collection centres had implemented the policy) and (3) after complete implementation of ferritin-guided donation intervals. As Sanquin had already started the implementation of the ferritin-guided donation intervals in November 2017, before approval from the Ethical Advisory Board for the FIND’EM study, we were unable to collect questionnaire data from donors at baseline. However, baseline data on other outcomes (Hb and ferritin levels, low-Hb deferral and donor return) are measured after ethical approval in stored samples, and a large majority of the donors (99%) provide their consent to the routine request to ‘make the unusable remainder of my donation available for medical scientific research in general’ (Fig. 2). Whole blood donors who visit one of the 50 fixed blood collection centres during a pre-selected week at mid-implementation or after complete implementation are asked to participate by completing questionnaires. This makes the current study an open cohort design study with repeated cross-sectional measures and new samples at each measurement. Donors registering at the registration desk of one of the collection centres during one of these time points will receive a leaflet with information on why this study is performed, explaining that upon participation, the donor is asked to fill in a questionnaire and participation is voluntary, the leaflet contains contact details of the research team in case of any questions and a link to the study website with additional information and frequently asked questions. The donor is asked to read the study information while waiting for their health check. After the check, the donors will be asked whether they have read the study information. If the donor decides to participate, an informed consent form will be signed and the donor physician or nurse will sign the form as a representative of the researcher. Donors who decide not to participate are asked to write down the reason for non-participation.

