The use of a stepped wedge cluster randomised trial approach allows to implement and simultaneously evaluate the policy. As data collection takes place at multiple time points during the implementation period, all blood collection centres contribute data under both the control and intervention condition. Furthermore, this design makes it possible to investigate the effects as if it was a randomised controlled trial by correcting for time and clustering of donors and blood collection centres. This design also introduces some challenges, including prolonged trial duration compared to a standard randomised controlled trial, time-varying confounding, instructing all parties involved, making sure each cluster is committed and performing the assigned policy, and communication with whole blood donors [14, 21]. Furthermore, the lack of blinding to the allocation for both participants and trial staff may introduce a risk of bias [22]. Recruitment bias for the questionnaire data is limited by inviting all eligible donors at the different measurement time points to participate. For other outcomes, all available information from donors who gave consent for their unusable remainder of the donation to be used for medical scientific research was used in the current study. Detection bias is expected to be minimal because outcome assessment does not include any judgement from the researchers [22]. For our sample size calculation, we considered multiple clustering effects that may be present in our study design. An individual autocorrelation coefficient will not affect our sample size as there are no repeated measurements from the same participants. As participants in the same cluster are more alike than participants in another cluster, we included an intraclass correlation coefficient of 0.10. Finally, it may be necessary to take into account a cluster autocorrelation coefficient. However, the cluster autocorrelation coefficient may be difficult to determine and the impact on the total sample size is probably limited [23]. Although the appropriate sample size calculation for stepped wedge designs is still subject of discussion, it is a potential limitation that we did not take into account a cluster autocorrelation coefficient in our sample size calculation. The setting of Sanquin as one organisation with multiple blood collection centres has some advantages in the execution of a stepped wedge cluster randomised trial compared to locally organised general practices or hospitals, for example. The blood collection centres are randomised to implementation steps and instructed to perform the assigned policy, with centralised organisation and monitoring. To our knowledge, this method has never been used in transfusion-related research. The effectiveness of the ferritin-guided donation interval policy on Hb and ferritin levels, Hb deferral rates, donor return rates and donor health likely has a delayed response, because (1) donors’ ferritin levels are only measured when they make a fifth donation and (2) the policy involves donation interval extension which delays follow-up. Delaying the implementation period of ferritin-guided donation intervals should therefore have minimal negative impact on the outcome of the study. Sanquin’s Ethical Advisory board approved the FIND’EM study protocol after the start of the implementation period and we were therefore not able to collect baseline questionnaire data in September 2017. Furthermore, this together with logistic constraints made it impossible to collect data at each implementation step. Therefore, we might have less detailed data on the effects of the new policy on the outcomes over time compared to a design with outcome measurements at each cross-over period. The secondary outcome donor health is measured at mid-implementation and after complete implementation. Investigating the effectiveness of the ferritin-guided donation intervals policy on donor health is limited to the use of questionnaire data collected at mid-implementation and after the implementation period. Data on ferritin levels is available at baseline, mid-implementation and after complete implementation of the policy.

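### The analysis of how the effect develops over time uses a calendar clock as effect modifier: the term is inestimable for donor health and, for the other outcomes, measures a change in calendar trend

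*Protocol article*

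**What the plan says.** The Data analyses section of the protocol article fixes three things.

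- The policy term: "All models include a binary variable indicating whether the observation was done before or after the start of the intervention".
- The time term, described as the time point of implementation and defined in parentheses as "fixed variable, time in months since the start of implementation period".
- The interaction: "To investigate how the impact of ferritin-guided donation intervals develops over time, the latter will also be included as an effect modifier".

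The models are to estimate "differences in Hb and ferritin levels, low-Hb deferral, donor return rates and donor health between intervention and control groups using data collected at baseline" as well as at the two later waves, so donor health is among the modelled outcomes.

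The Study population section sets three waves. The first precedes the rollout, the second is given as "mid-implementation (when 55% of blood collection centres had implemented the policy"), and the third is placed "after complete implementation of ferritin-guided donation intervals". For questionnaires it says "we were unable to collect questionnaire data from donors at baseline". The Discussion repeats this limit, leaving only the mid wave and the last one: "Investigating the effectiveness of the ferritin-guided donation intervals policy on donor health is limited to the use of questionnaire data collected at mid-implementation and after". It also concedes less detail on effects over time, but it does not withdraw or restrict the interaction for any outcome.

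**The concern.** The article says twice, in Study population and in the Discussion, that the effect will be delayed. The interaction is the only planned analysis that addresses this. A delayed effect develops with the time a cluster has spent under the policy. On the calendar reading, the modifier takes one value for every cluster at a given wave. At the last wave it treats a step 1 cluster (about 24 months under the policy) and a step 4 cluster (under one month) alike.

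Two consequences follow. For donor health the specified model has more parameters than the data can separate. The result would then depend on which column the software drops. For the other outcomes a number will be produced, but it can be read as growth or fading of the policy effect when it reflects season, laboratory or donor mix between periods.

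**Working it through.** **Inputs from the article.** Study design: 8 clusters crossed in November 2017 (month 0), 4 in May 2018 (6), 4 in October 2018 (11), 4 in March 2019 (16), 3 in October 2019 (23) and 6 in November 2019 (24), in total 29. Discussion: baseline September 2017 (month -2). Trial status: last wave at the end of November 2019 (about month 24.5). Sample size calculations: SD 54 ng/mL, intraclass correlation (ICC) 0.1, about 7500 donors per wave, so 7500/29 ≈ 259 per cluster.

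**Assumptions.** The mid-wave date is not stated. With 16 clusters exposed it must lie between months 11 and 16; 12.5 and 15 are used below. ICC is varied from 0.01 to 0.1.

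**The plan's own figure.** (8 + 4 + 4)/29 = 16/29 = 55.2%, which matches the stated 55%. The article words it as a share of centres; the cluster count reproduces it.

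**Cells available (number of clusters).**

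| Wave | Control | Exposed | Donor health measured |
|---|---|---|---|
| Baseline | 29 | 0 | no |
| Mid | 13 | 16 | yes |
| Last | 0 | 29 | yes |

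**Planned fixed part.** Mean = a + b·t + d·X + g·X·t, with t in calendar months and X = policy on/off: four parameters.

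**Donor health.** With t1 the mid wave and t2 the last wave:

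- mid, control: a + b·t1
- mid, exposed: a + b·t1 + d + g·t1
- last, exposed: a + b·t2 + d + g·t2

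The last two differ by (b + g)(t2 − t1), so only the sum b + g is identified. The first two differ by d + g·t1. Neither g nor d can be separated. The design matrix has rank 3 for 4 columns at every mid date tried from 11.5 to 15.9. A random cluster intercept does not change this. Without the interaction the model has rank 3 of 3, so the on/off effect is estimable.

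**Haemoglobin, ferritin, deferral, return.** Four cells, four parameters, rank 4 of 4. In terms of cell means,

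g = (exposed last − exposed mid)/(t2 − t1) − (control mid − control baseline)/(t1 − t0).

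The two slopes come from different calendar periods. With wave as a category the policy-by-wave model has rank 4 of 6 and no interaction is estimable, so g rests entirely on a linear secular trend.

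**Illustration 1: effect grows linearly with own exposure to 4 ng/mL at 24.5 months, no period shift.** With mid at 12.5, mean exposure among exposed clusters is (8×12.5 + 4×6.5 + 4×1.5)/16 = 8.25 months. At the last wave it is (8×24.5 + 4×18.5 + 4×13.5 + 4×8.5 + 3×1.5 + 6×0.5)/29 = 12.60. Calendar time advances 12 months while mean exposure rises 4.35, because new clusters join. From cell means, g × 24.5 = 4 × 4.35/12 = 1.45. Generalised least squares with the random intercept gives 1.43, and 1.20 to 1.27 with mid at 15.

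**Illustration 2: constant effect of 4, plus a 2 ng/mL shift in all clusters at the last wave.** g × 24.5 = 2 × 24.5/12 = 4.08 (mid 12.5) or 2 × 24.5/9.5 = 5.16 (mid 15). The true value is 0. The standard error of the planned term on this scale is 2.7 to 3.1.

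**Replacement: wave as a category, policy, months since own crossover.** Rank is 5 of 5 with three waves and 4 of 4 for donor health. The standard error of the exposure term × 24.5 is 2.0 to 2.1 with three waves. With two waves and the same SD and sample size it is 2.9 (ICC 0.01) to 6.1 (ICC 0.1).

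**Shape check.** If the effect is 0 until 6 months and 4 afterwards, the linear replacement predicts 5.8 to 6.3 at 24.5 months instead of 4.

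**The case against.** **The wording is ambiguous.** The time variable could mean the month in which a cluster crossed over, with the parenthesis giving only unit and origin. The interaction would then be estimable (rank 6 of 6 with three waves and 5 of 5 for donor health, with wave in the model). This stands as a possible reading. The parenthesis points more naturally to a common clock, however, and the Discussion says the design corrects for time. On the crossover-month reading the stated model would contain no calendar adjustment at all. The sentence needs correcting either way.

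**Donor health may not have been meant.** The interaction sentence names no outcome, and the two-wave limit is disclosed. True, but the section lists donor health among the modelled outcomes and nothing exempts it.

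**The illustrations are constructed.** This is right. The 2 ng/mL shift has no source in the article. The 4.1 to 5.2 comes from scaling to 24.5 months; between the mid and last waves the false change is 2. Growth to 4 at 24.5 months is not the Sample size section's 4 ng/mL over 6 months. The replacement recovers both truths because both lie inside its model. The figures show direction and mechanism, not expected bias.

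**The replacement has weaknesses.** Linear exposure misfits a delayed effect, and the donor-health term is imprecise. The article does not say that the 2a/2b and 3a/3b splits were random, and one step 3 cluster crossed late, so exposure differences are partly not randomised. All of this stands and shapes the fix.

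**Conclusion.** The point holds and should be fixed, but it concerns a supplementary term. A reader might infer that the trial cannot estimate the policy effect, or its effect on donor health. The documents do not support that: the on/off model has full rank for every outcome. Nor is the absence of controls at the last wave a fault, since every stepped wedge ends that way. It would also go too far to say that the interaction cannot be estimated for haemoglobin, ferritin, deferral or return. It can, under a linear secular trend.

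What is supported, on the calendar reading:

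- For donor health the interaction is not estimable, whatever the SD, ICC or mid-wave date.
- For the other outcomes it measures change in calendar trend, not growth with exposure. Its size is illustrated by 1.2 to 1.4 in place of 4, and 4.1 to 5.2 in place of 0, under the assumed dates and shifts.

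**What to change.** In Data analyses:

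1. Enter measurement wave as a categorical fixed effect.
2. Replace the calendar modifier with the cluster's own time since crossover at the measurement week, with controls as reference. A few categories are preferable to a linear term because a delay is expected. For example, 0–2, 3–9, 10–15 and over 15 months: with the mid wave at 12.5 these hold 4, 4, 8 and 0 clusters at mid and 9, 4, 4 and 12 at the last wave.
3. State that at the last wave the effect is identified only by comparing clusters with different exposure lengths.
4. State that for donor health this term rests on two waves, is imprecise, and is exploratory.
5. Add a sensitivity analysis by randomised step, and say how actual crossover dates sit with the intention-to-treat approach.

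The cost is a few sentences. Crossover dates are known and no new data are needed. The price is an assumed shape over exposure, some loss of precision from categories, and reliance on exposure differences not stated to be randomised within steps 2 and 3.
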